### Fidelity/confidentiality

Data will be collected and stored using Research Electronic Data Capture (REDCap), a secure, online data collection tool (access provided by Lawson Health Research Institute in London, ON). Raters will also use REDCap to administer assessments and capture participant data. For assessments that are required to be completed on paper forms (i.e., executive function measures), pertinent data (i.e., Z-scores) will be inputted by the research personnel into REDCap. For assessments that are self-rated, participants will complete a REDCap-generated survey. Collected data will be continually reviewed by the research staff to ensure accuracy of completion. All changes in REDCap will be automatically logged to ensure the fidelity and integrity of the study data. As REDCap is a secure, online data-entry and repository tool, it will be available for access in real time by researchers in both London, ON, and Montreal, QC.

### Participant retention efforts

Exit interviews will be conducted at week 12 for all withdrawn participants willing to attend. These exit interviews will include all week 12 study procedures. Study participants will be remunerated at a rate of CAD$20 per assessment visit for the main study and CAD$80 per visit if participating in the MRI sub-study. To prevent undue burden, participants will be offered regular breaks during study assessment procedures as well as flexibility of attending these procedures either over one whole day or two consecutive half days, based on their personal preference. It is expected that the baseline assessment procedure will need 6–8 h of participant time while follow-up assessments at 12 and 26 weeks will each be 4–6 h long. If a participant chooses to withdraw at any time during the study, they will be allowed to do so. However, the research staff will try and ascertain from the participant the reason for withdrawal and document these reasons. If a participant is unable to adhere completely with this study protocol, all reasonable efforts will be made to accommodate their needs and requests. If there is significant deviation (greater than 1 week from an expected assessment point), they will be considered as a withdrawal from the study. All such withdrawals and deviations will be recorded on REDCap.

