For the purpose of further exploration of the beneficial effects of SSM we plan to conduct a study with the primary hypothesis that SSM, compared to an active control, will lead to a significant improvement of depressive symptoms in participants with LLD at 12 weeks and that this effect will persist at 26 weeks. We will also examine a secondary hypothesis that SSM leads to an improvement in other variables including executive function. Exploratory outcomes will be changes in anxiety, quality of life, gait, and central as well as peripheral immune function.

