## Methods/Design

### Aims

The objective of this study is to compare the effects of *Sahaj Samadhi* meditation (SSM) on related psychological and biological outcomes against an active control, the Health Enhancement Program (HEP).

Primary outcome: the primary outcome measure will be change in depression scores in the SSM arm compared to HEP at 12 weeks. We will also assess the percentage of SSM participants who will meet the clinical criteria for remission compared to HEP at 12 weeks. Lastly, we will assess whether participants in the SSM arm will continue to have reduced depression scores at the 26-week follow-up.

Secondary outcome: the secondary outcome measure will be a neuropsychological battery for assessing executive function with an emphasis on planning and organization ability, at the primary endpoint of 12 weeks.

Exploratory outcomes: for a complete list of such outcomes and their associated hypotheses, please refer to Table 1.

**Table 1 Tab1:** Objectives and hypotheses

Objective		Hypothesis
Primary		
1.	Using a 12-week RCT, assess whether SSM improves depressive symptoms in LLD compared to an active-control condition; HEP	(a) In participants with LLD, SSM participants, compared to HEP controls, will have a greater reduction in depressive symptoms from baseline to 12-week follow-up, as measured by the Hamilton Rating Scale for Depression (HRSD-17) (b) Compared to HEP, a higher percentage of SSM LLD participants will meet the clinical criteria for remission, as defined by HRSD-17 scores < 8 at the 12-week follow-up
Secondary		
2.	To assess the effects of SSM on a specific executive function, i.e., organization ability in LLD	In participants with LLD, compared to HEP, SSM will be associated with better organization ability, at 12-week follow-up
Exploratory		
3.	To assess the effects of SSM on other executive function domains in LLD	In participants with LLD, compared to HEP, SSM will be associated with better executive functions, at 12-week follow-up
4.	To assess the effects of SSM on global cognition in LLD	In participants with LLD, compared to HEP, SSM will be associated with better global cognition, at 12-week follow-up

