### Design

The study is a two-site (London, Ontario (ON), Canada, and Montreal, Quebec (QC), Canada), 12-week, RCT in which raters, clinicians, and care providers will be blinded to participant group allocation and participants will be blinded to study hypotheses. Participants will attend three assessment sessions (baseline/0 weeks, 12 weeks, and 26 weeks) in a research-hospital setting.

Participants will attend either SSM or HEP for four consecutive days of training for 2 h per day. Following the 4 days of initial training, participants will attend 1-h weekly follow-up sessions of HEP or SSM for 11 subsequent weeks. See Fig. 1 for an outline of the study assessments and the intervention schedule. A subset of participants will be recruited in an exploratory sub-study examining neurobiological brain changes associated with depression and any changes in depressive symptoms, with magnetic resonance image (MRI) scanning to take place at the 0-week and 12-week time points. Patients will also be offered the opportunity to participate in sub-studies designed to assess the effects of SSM versus HEP on (1) gait as measured by a standardized gait mat, (2) peripheral inflammatory markers, (3) sleep as measured by a proprietary Actigraph, and (4) change in level of mindfulness, awareness as well as shifts in level of consciousness.

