## Outcomes

A screening assessment will be conducted to determine a participant’s eligibility for the study. Following completion of the informed consent process, baseline assessments will be completed. Demographics collected at baseline include age, biological sex, and self-identified gender, ethnicity, height, weight, along with hip and waist circumference, as well as housing, marital, and employment status. A medication record will be collected as per participant report along with reconciliation from pharmacy records.

The following scales will be administered at the baseline assessments (a complete list of the assessments to be completed at different time points can be found in Table 2).

**Table 2 Tab2:** Primary and secondary outcome measures for all participants; weeks 0–26

Evaluations	Enrollment	Randomization and interventions’ start	Follow-ups	
	Week 0	Week 1	Week 12	Week 26
Primary outcome: depression				
HRSD-17	✓		✓	✓
Secondary outcome: executive function				
WAIS-IV–Digit Span	✓		✓	✓
D-KEFS Verbal Fluency Test	✓		✓	✓
California Verbal Learning Test-II, Short form	✓		✓	✓
Rey-Osterrieth Complex Figure–Copy Trial	✓		✓	✓
D-KEFS Color Word Test Conditions 1–3	✓		✓	✓
Exploratory and screening measures:				
To be administered by examiner:				
MINI-COG	✓			
PHQ-9	✓		✓	✓
ATHF	✓			
Mini International Neuropsychiatric Interview	✓			
CIRS-G	✓			
CGI (Severity portion only)	✓			
CGI (entire scale)			✓	✓
Athens Insomnia Scale	✓		✓	✓
MoCA (London only)	✓			✓
WAIS-IV–Test of premorbid functioning	✓			
To be completed by participant:				
FES-I (London only)	✓		✓	✓
PHQ-9	✓		✓	✓
GAD-7	✓		✓	✓
GAI	✓		✓	✓
WHO DAS 2.0	✓		✓	✓
EQ-5D-5 L	✓		✓	✓
TTO	✓		✓	✓
TSES	✓		✓	✓
PCI			✓	✓
SPWB	✓		✓	✓
FFMQ	✓		✓	✓
Likert scale			✓	
Participant-reported side effects			✓	✓
Other data collected:				
Assessment of eligibility	✓			
Informed consent	✓			
rs-fMRI/MRI/sMRI (only if enrolled in MRI sub-study)	✓		✓	
Demographics (including medications)	✓			
Changes in demographics (including medications)			✓	✓
Acti-watch^a^ (Montreal only)	✓		✓	
Gait (London only)	✓		✓	✓
Blood draw (London only)	✓		✓	

^a^this measure is administered 2 weeks prior to week 0 and 2 weeks following week 12

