### Primary outcomes

The HRSD-17 scores at baseline, 12-week, and 26-week follow-up of participants assigned to SSM and HEP will be compared using linear mixed models: 2 (SSM vs HEP) × 3 (0 weeks, 12 weeks, 26 weeks). This approach will account for the clustering of observations, since both SSM and HEP will be delivered in a group setting. Next, we will evaluate whether a greater proportion of participants assigned to SSM, compared to HEP, achieve depression remission (defined as a HRSD-17 score ≤ 7 at the 12-week follow-up) using generalized linear mixed models (hypothesis 1B).

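### No week-26 HRSD-17 is described for participants who withdraw, so the 26-week persistence analysis relies on a missing-at-random assumption for them

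*Protocol article*

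**What the plan says.** The section on participant retention efforts sets the follow-up of leavers. "Exit interviews will be conducted at week 12 for all withdrawn participants willing to attend", and "These exit interviews will include all week 12 study procedures", so the HRSD-17 is sought from them at week 12. The same section adds an administrative route into the withdrawn group: "If there is significant deviation (greater than 1 week from an expected assessment point), they will be considered as a withdrawal from the study". It mentions week 26 only when it gives the length of the follow-up visits, and it does not say whether a withdrawn person is invited then.

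The week-26 score has several roles:

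- The closing paragraph of the Background states the primary hypothesis as a benefit at 12 weeks "and that this effect will persist at 26 weeks".
- The Aims section, under the primary outcome, says "we will assess whether participants in the SSM arm will continue to have reduced depression scores at the 26-week follow-up".
- The analysis section on primary outcomes says "The HRSD-17 scores at baseline, 12-week, and 26-week follow-up of participants assigned to SSM and HEP will be compared using linear mixed models", with weeks 0, 12 and 26 as the three times.
- Table 1, objective 7, lists the 26-week comparison of the arms as exploratory.

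The general schedule covers week 26. The Design section says "Participants will attend three assessment sessions (baseline/0 weeks, 12 weeks, and 26 weeks) in a research-hospital setting", and Table 2, titled "Primary and secondary outcome measures for all participants; weeks 0–26", ticks the HRSD-17 at week 26.

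**The concern.** Leaving the study can depend on the assigned programme and on mood. If leavers' week-26 scores are not sought, the mixed model predicts their late course from their earlier scores and from people who stayed. That prediction is right only if, given the scores already seen, leavers would have done as well as continuers. If they do worse in a way that narrows the difference between arms, the estimated persistence is too large.

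Two features of the text widen the gap. A person who withdraws after week 12 has passed the only exit time point and has no further visit described. A willing person who is merely late for an assessment is classed with those who left. At stake is the 26-week claim, because a score that was not collected cannot be recovered by a later analysis plan.

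**Working it through.** **Number of leavers**

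- Planned attrition (Sample size section): 16% of 192 = 30.7, about 31 people. Completers: 192 × 0.84 = 161.3, which reproduces the stated figure of approximately 160.
- Progress count (Trial progress section): 26 completed + 7 in the intervention + 11 withdrawn = 44. 11/44 = 25%, and 0.25 × 192 = 48. Of those no longer in the intervention, 11/37 = 29.7%, about 57 of 192. The section does not say when people left or whether they attended the exit visit, so these are projections and not forecasts.

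**What a week-26 visit for leavers would change**

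The benefit in continuers is set at 2.6 points, the protocol's detectable difference. The remaining assumptions are not in the documents:

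- continuers have that benefit at both weeks 12 and 26, and leavers have none at either;
- the week-12 to week-26 correlation is 0.6, with equal SDs;
- withdrawal is equal by arm;
- the same leavers attend both visits.

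Let d be the proportion withdrawn and a the proportion of leavers attending.

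- Difference over all randomised: 2.6 × (1 − d).
- Week-12 estimate: E12 = 2.6 × (1 − d) / (1 − d + a·d).
- Week-26 estimate without leavers' week-26 scores: 2.6 + 0.6 × (E12 − 2.6).
- Week-26 estimate with those scores: the same expression as E12.
- Overstatement removed by the extra visit: (1 − 0.6) × (2.6 − E12).

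For example, at d = 0.25 and a = 0.5, E12 = 2.6 × 0.75/0.875 = 2.23. Without week 26 the estimate is 2.6 + 0.6 × (2.23 − 2.6) = 2.38, and with it 2.23.

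| Withdrawn | Leavers attending | All randomised | Without week 26 | With week 26 | Removed | Left over |
|---|---|---|---|---|---|---|
| 25% | none | 1.95 | 2.60 | 2.60 | 0 | 0.65 |
| 25% | half | 1.95 | 2.38 | 2.23 | 0.15 | 0.28 |
| 25% | all | 1.95 | 2.21 | 1.95 | 0.26 | 0 |
| 16% | none | 2.18 | 2.60 | 2.60 | 0 | 0.42 |
| 16% | half | 2.18 | 2.46 | 2.37 | 0.09 | 0.19 |
| 16% | all | 2.18 | 2.35 | 2.18 | 0.17 | 0 |

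**Range.** At 25% with all attending, the amount removed is (1 − correlation) × 0.65: 0.39 at a correlation of 0.4 and 0.13 at 0.8. If leavers keep half the benefit, the shortfall halves and the amount removed at a correlation of 0.6 is 0.4 × 0.325 = 0.13. Other patterns, such as benefit that fades only after week 12, would give other figures.

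**The case against.** The strongest reply is that this is silence in a condensed article. The Discussion calls the text a brief outline, and the Trial status section points to a fuller internal protocol. Nothing forbids a week-26 visit after withdrawal, and the Design section and Table 2 schedule week 26 for participants in general. This stands against any claim that the scores are never collected. It does not remove the point, because the retention section sets the specific rule for leavers and names week 12 alone.

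A reader might infer that anyone who stops attending sessions is withdrawn. The text does not say so. It promises to accommodate incomplete adherence, records withdrawals and deviations as separate things, and uses 75% attendance only as willingness at entry. The one automatic rule concerns the timing of assessments.

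A reader might also infer that the 26-week result describes only those who stayed. A likelihood-based mixed model keeps leavers' baseline scores and any week-12 exit score, so the fair statement is dependence on missing at random.

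It is also true that Table 1 makes week 26 exploratory, that the exit visit supports the 12-week endpoint, and that those who leave in weeks 13 to 25 have largely finished the group sessions. These facts lower the stakes but leave the 26-week gap in place.

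**Conclusion.** The point holds in a limited form. The article describes no week-26 HRSD-17 for withdrawn participants, some of whom may be withdrawn only because an assessment fell outside its window. The persistence analysis therefore relies on missing at random for about 31 of 192 people as planned, or about 48 if the 25% progress count held. The 12-week endpoint is largely protected.

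Under the stated assumptions, collecting week 26 removes 0 to 0.26 points of overstatement at 25% withdrawal and 0 to 0.17 at 16%. The largest of these is a tenth of the 2.6-point design difference (0.26/2.6). It would be tempting to quote the full 0.65-point overstatement at 25%. That figure arises only when no leaver attends even week 12, and on the assumption that the same people attend both visits an added week-26 visit would then change nothing. The existence of the gap is well supported by the text; its size is illustrative.

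**What to change.** In the section on participant retention efforts:

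- State that stopping the SSM or HEP sessions, or missing an assessment window, is not withdrawal from assessment.
- Offer the HRSD-17 at week 26 as well as week 12 to everyone who has not refused further contact, including those who leave after week 12.

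In the analysis section on primary outcomes, say that these scores enter the mixed model under the randomised arm. If the internal protocol already provides for this, one sentence in the article is enough.

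The cost is protocol wording, one extra invitation and one CAD$20 payment per leaver: 31 × 20 = CAD$620 to 48 × 20 = CAD$960 if all attend. The HRSD-17 interview takes 20 to 30 minutes, so the full follow-up battery is not needed. The downside is some added contact with people who have stopped. With 44 of 192 enrolled at the progress date, most participants could still be covered.

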## Statistical analysis

### Sample size

Recruitment is expected to occur over a 26- to 36-month period at a rate of two participants per week (total of *n* = 192). See Fig. 1 for a schematic diagram. It is estimated that a sample of 192 participants will offer sufficient power for the primary outcome (HRSD-17). This sample size calculation is based on an estimated effect size from our pilot data from participants with LLD undergoing SSM or treatment as usual (TAU). Over the 12-week intervention, participants in the SSM group had significant change in HRSD-17 scores when compared to the TAU group (2.66 (95% CI 0.26 to 5.05) point greater reduction; Cohen’s D = 0.61, *p* = .030). Assuming an average cluster size of 4–10 participants and a 1:1 allocation between the SSM and HEP groups, 192 participants will allow us to observe a 2.6-point difference in HRSD-17 scores between the two groups at a two-tailed α = 0.05 and 1 − β = 0.80. A 2.5-point difference is considered to be clinically significant among consensus expert reports and the Food and Drug Administration (FDA) considers it a minimum standard [74]. A 16% rate of attrition for this study is a conservative estimate based on our previously observed 13% attrition rate in the SSM versus the TAU study. As such, it is predicted that approximately 160 of the planned 192 recruited participants will complete the study and we will still have adequate statistical power.

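### The protocol counts a visit more than 1 week off schedule as a study withdrawal, which treats a late assessment like a true withdrawal and may cost week-12 and week-26 HRSD-17 data

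*Protocol article*

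**What the plan says.** The rule stands in the protocol article under Participant retention efforts: "If there is significant deviation (greater than 1 week from an expected assessment point), they will be considered as a withdrawal from the study". It applies to every expected assessment point. The Design section sets these: "Participants will attend three assessment sessions (baseline/0 weeks, 12 weeks, and 26 weeks".

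The same section has three provisions that bear on the rule:

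- For participants who cannot adhere fully, "all reasonable efforts will be made to accommodate their needs and requests".
- "Exit interviews will be conducted at week 12 for all withdrawn participants willing to attend", and "These exit interviews will include all week 12 study procedures". The HRSD-17 is one of those procedures (Table 2).
- "All such withdrawals and deviations will be recorded on REDCap".

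The primary analysis (Statistical analysis, Primary outcomes) takes HRSD-17 at all three times, and the arms "will be compared using linear mixed models: 2 (SSM vs HEP) × 3 (0 weeks, 12 weeks, 26 weeks". The Sample size section assumes 16% attrition and concludes that "it is predicted that approximately 160 of the planned 192 recruited participants will complete the study and we will still have adequate statistical power".

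**The concern.** Three different events share one label: a late assessment, stopping the intervention, and leaving the study. A participant assessed eight days late at week 12 is willing and assessable, yet by the rule has withdrawn. Two kinds of data are then at risk.

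- **Week 12, the primary endpoint.** A late participant has no in-window value. The exit assessment is placed at week 12, and the text does not say whether a visit after the window qualifies.
- **Week 26, where persistence of the effect is judged.** A participant withdrawn at week 12 has no reason to be called back, and no exit assessment is offered at week 26.

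The loss would follow from something that happens after randomisation. In depressed people aged 60 to 85 who face follow-up visits of 4 to 6 hours, lateness could plausibly go with low mood or poor adherence. If it depends on current, unobserved mood, a mixed model does not correct for it. The rule also adds attrition that the trial could avoid.

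**Working it through.** **1. The passages side by side**

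| Situation | Status under the rule | Week-12 HRSD-17 | Week-26 HRSD-17 |
|---|---|---|---|
| Leaves before week 12, willing to be assessed | Withdrawn | Offered through the exit assessment | None offered |
| Attends week 12 more than 1 week late | Withdrawn | Unclear: the exit assessment is set at week 12 | None offered |
| On time at week 12, more than 1 week late at week 26 | Withdrawn | Observed | Unclear: no equivalent provision |

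The first row is covered at week 12. The second and third are not clearly covered, although those participants are willing to attend.

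**2. The plan's own attrition figure**

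192 × (1 − 0.16) = 161.3, which agrees with the stated figure of about 160.

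**3. Calibrating power**

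Inputs from the Sample size section: difference 2.6 points, two-sided α 0.05, power 0.80, pilot effect 2.66 points with Cohen's d 0.61, clusters of 4–10. No intraclass correlation (ICC) is stated.

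- Implied SD = 2.66 / 0.61 = 4.36.
- Unclustered n per arm = 2 × (4.36 × 2.80 / 2.6)² ≈ 44.2.
- Design effect at which 80 completers per arm give exactly 80% power = 80 / 44.2 = 1.81.
- Implied ICC = (1.81 − 1) / (m − 1) = 0.27, 0.14 or 0.09 for m = 4, 7 or 10.

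These ICCs are assumptions, chosen so that the plan's 80% holds at about 160 completers.

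**4. Illustration: a further 10% of completers lost (assumed rate)**

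161.3 × 0.90 ≈ 145.

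- *Design effect held at 1.81:* 2.80 × √(145/161) = 2.66. Power = Φ(2.66 − 1.96) ≈ 0.76.
- *Clusters shrink with the loss:* with m = 3.6, 6.3 or 9.0 the design effect, 1 + (m − 1) × ICC, is about 1.70, 1.72 or 1.72. Effective n per arm = 72.5 / design effect ≈ 42.6, 42.2 or 42.1. Power = Φ(2.80 × √(effective n / 44.2) − 1.96) ≈ 0.78 in each case.

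So power falls from 80% to about 76–78%.

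**5. Withdrawals so far**

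Trial progress reports 11 withdrawals among 44 enrolled: 11/44 = 25% (exact 95% CI 13% to 40%). If the true rate were 16%, 11 or more would occur with probability 0.083. This is above plan, but not clearly so. No reasons are given, so none of it can be attributed to this rule.

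**6. Direction of a possible bias (every input assumed)**

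A simulation compared observed means with a true difference of 2.6, SD 4.36 and about 8–13% of visits lost.

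- Lateness unrelated to outcome: the estimate stays at about 2.6.
- Worse participants late in both arms: about 2.4 to 2.5.
- That link in one arm only: about 2.1 to 2.9.

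This shows that bias can go either way. It does not estimate the bias of the planned mixed model.

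**The case against.** The strongest reply is that nothing in the article says off-window or withdrawn participants' HRSD-17 values are deleted or left out of the analysis. Deviations are recorded, the mixed model needs no complete cases, and visit windowing usually belongs to the SAP, which is not at hand. This stands. A reader might infer that usable primary-outcome data are discarded and the intention-to-treat comparison is broken, but the text does not support that.

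The exit assessment is open to every withdrawn participant, which includes those withdrawn by this rule. It is a partial safeguard for the 12-week endpoint. What remains is its timing at week 12 and the absence of anything similar at week 26.

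A reader might also infer that the rule makes missingness depend on how the participant is doing. That is plausible, but the article gives no reasons for late visits and no rate. The mixed model is valid if missingness depends only on observed data.

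The 16% attrition may already include withdrawals of this kind, so it is not established that the sample size fails to allow for them.

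The promise of accommodation softens the rule in practice, but the rule follows it without an exception. Nor can an SAP fully repair the matter: it can decide how to use values that were collected, but it cannot recover a week-26 visit that was never held.

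**Conclusion.** The point holds as a defect in the conduct rule. The protocol fixes a rule that makes lateness a withdrawal. Followed as written, it would end follow-up before week 26 for willing participants and may lose week-12 values. It also sits badly with the accommodation and exit-assessment provisions of its own section, and the passages need to be reconciled.

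The size is unknown, because no off-window rate is given. The fall in power to about 76–78% rests on an assumed 10% loss on top of the planned 16%, and on ICCs inferred from the plan's own 80%. Bias is a plausible risk, not a demonstrated one. The change is well worth making because it is cheap and the lost visits cannot be recovered later. The documents do not support calling the primary analysis invalid.

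**What to change.** Replace the sentence with a rule along these lines:

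- A visit more than 1 week from its expected date is a protocol deviation.
- The assessment is still done and its actual date recorded.
- The value stays in the primary mixed model.
- The week-26 visit is still scheduled.
- Withdrawal is reserved for participants who choose to leave the study.

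State also that the exit assessment may take place after the week-12 window. Use the 1-week window only in a sensitivity analysis restricted to in-window visits.

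The cost is a short protocol change and one sensitivity analysis. The downside is slightly more spread in actual assessment times around weeks 12 and 26, which the recorded dates make visible and the sensitivity analysis tests.
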